#### Secondary Outcomes

Secondary outcomes include changes from baseline in oxygen desaturation index, supine AHI, total sleep time, average heart rate, mean SpO_2_, the percentage of time with oxygen saturation below 90%, obtained from PSG; neck, waist, and hip circumference; BMI values; forced vital capacity and forced expiratory volume in 1 second values; WHOQOL-BREF score; CPAP adherence; as well as total cholesterol, triacylglycerols, HDL cholesterol, LDL cholesterol, and non-HDL cholesterol values.

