### Inclusion Criteria

Participants will be eligible if they are male patients, aged 30-60 years, have newly diagnosed OSA with an AHI ≥15 episodes per hour, are indicated to CPAP therapy, and are interested in our adjunct tele-RHB program.

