### Exclusion Criteria

Participants are excluded if they have another type of OSA treatment, chronic corticosteroid therapy or long-term oxygen therapy; they are also excluded if they have at least one of the following health problems: central sleep apnea, chronic obstructive pulmonary disease III or IV, severe pulmonary hypertension, New York Heart Association III or IV, acute coronary syndrome, heart failure, ejection fraction <40%, electrocardiographic-documented heart arrhythmia, severe heart valve disease, cerebrovascular disease, psychiatric disease, and physical disability; in addition, they will be excluded if they do not cooperate during the intervention or do not follow the tele-RHB program and CPAP therapy protocol.

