### Recruitment, Enrollment, and Procedure

The patients who meet the inclusion criteria will be recruited from the Sleep Centre of the FNUSA-ICRC. The details of the study overview are shown in Table 1. On the first visit, patients will undergo polysomnography (PSG), blood sampling for lipid profile, and completion of the Epworth Sleepiness Scale (ESS) with a known score. Those who are found to have moderate to severe OSA will be contacted for further intervention alongside the standard CPAP therapy. These patients will be verbally informed and will receive an information leaflet about the ongoing study of the 12-week tele-RHB program. Then, they will complete anthropometric and spirometric examinations, measurements of maximal inspiratory mouth pressure (MIP) and maximal expiratory mouth pressure (MEP) as well as body composition, 6-minute walk test (6MWT), and QoL questionnaires in the Cardiovascular Rehabilitation Clinic at the University Hospital Brno (CRC-UHB). After that, during the interview with a physiotherapist, participants will receive detailed and comprehensive information regarding their possible participation in the study. Then, potential participants will be given at least 24 hours to decide before signing the informed consent.

On the second visit, patients who agreed to participate in the study will sign the informed consent form and will be then randomized 1:1 to the intervention or control group.

On the third visit, participants of both groups will undergo individual titration of CPAP therapy at the Sleep Centre of the FNUSA-ICRC. The intervention group will subsequently receive education about the tele-RHB program, along with theoretical and practical instruction on its individual components in the CRC-UHB. Participants of the intervention group will also receive a training brochure containing information needed for the tele-RHB program with remote supervision by a physiotherapist.

After the completion of the 12-week tele-RHB program, on the fourth visit, participants of both groups will undergo the same examinations and measurements as those conducted at the baseline, at the Sleep Centre of the FNUSA-ICRC and in the CRC-UHB.

After 1 year from the 12-week tele-RHB program’s completion, on the fifth visit, participants of both groups will undergo the same examinations and measurements as they did at the baseline in both health facilities.

**Table 1 table1:** An overview of the study flow.

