All participants’ CPAP devices will be regularly remotely monitored by a Sleep Centre medical doctor to track CPAP compliance and adherence to treatment during their sleep-at-home conditions. Participants will use one of the following devices: AirSense 10 AutoSet (ResMed Inc) or Prisma 20A Auto CPAP (Löwenstein Medical Technology GmbH + Co. KG).

Participants will have laboratory blood tests with the intention of finding out the current values of their lipid profile. Values of the total cholesterol, triacylglycerols, high-density lipoprotein (HDL) cholesterol, low-density lipoproteins (LDL) cholesterol, and non-HDL cholesterol will be detected.

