## Discussion

OSA is a severe global problem [6,7,38], negatively affecting the QoL and its various aspects [8,38]. Furthermore, although CPAP therapy is currently considered the gold standard of treatment [38], adherence to its long-term use is low [39]. According to Aardoom et al [40], about 30% to 80% of patients with OSA are nonadherent to their CPAP therapy. However, CPAP adherence and therapy compliance can be improved by a telemedicine-based approach (ie, eHealth) containing regular teleconsultations via video calls [41]. According to Hnatiak et al’s [42] opinion, an additional therapy consisting of the implementation of the tele-RHB program could also improve the severity of OSA or even help with adherence to CPAP therapy. In addition, our comprehensive program, consisting of effective elements of rehabilitation, includes aerobic exercise training [17,18], oropharyngeal training [19], and respiratory muscle training [21], along with recommendations focusing on nutrition, lifestyle, and behavior changes [14-16].

The development of this tele-RHB program for the examined population was based on currently available knowledge. The comprehensive tele-RHB program was designed according to information about effective additional treatment options for OSA mentioned earlier. The study included only middle-aged and older male adults due to the risk of more frequent OSA occurrences in these individuals [3,4]. Thus, significant risk factors for the development of OSA also include middle [4] or older age, smoking [3], and obesity [3,4].

A possible limitation may be the lack of direct physiotherapist supervision during the remotely monitored intervention in a home-based setting. According to Hnatiak et al [42], regular communication of participants with physiotherapists during the intervention should help the standard course of the intervention. Thus, we assume that the completion of this intervention will produce interesting results that will help the further development of additional therapeutic options for OSA.

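### CPAP adherence is listed as a change from baseline although CPAP starts after randomisation, and it would be compared only in men selected on that same adherence

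*Protocol article*

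**What the plan says.** Under Secondary Outcomes, one sentence with a single lead-in, "Secondary outcomes include changes from baseline in oxygen desaturation index", runs through the whole list and includes "WHOQOL-BREF score; CPAP adherence; as well as total cholesterol". As written, CPAP adherence is a change from baseline.

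The visit schedule is in Recruitment, Enrollment, and Procedure and in Table 1. Baseline examinations are at the first visit. At the second visit, consenting patients "will be then randomized 1:1 to the intervention or control group". CPAP comes after that: "On the third visit, participants of both groups will undergo individual titration of CPAP therapy". Under Inclusion Criteria, participants must "have newly diagnosed OSA with an AHI ≥15 episodes per hour", and Exclusion Criteria rules out other OSA treatment. Adherence is to be read from the home devices, which are monitored remotely in all participants "to track CPAP compliance and adherence to treatment during their sleep-at-home conditions" (Measurements and Examinations).

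Exclusion Criteria also removes men who "do not follow the tele-RHB program and CPAP therapy protocol", without giving a threshold. Study Design names a per-protocol analysis. Statistical Analysis plans a paired t test of baseline against post-intervention values within each group, and an unpaired t test between groups. The Discussion reports a published opinion that such a programme "could also improve the severity of OSA or even help with adherence to CPAP therapy".

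**The concern.** There are two separate problems.

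The first is a contradiction between the outcome and the schedule. A change from baseline needs a pre-treatment value, and a man who has not yet been given CPAP has no adherence to record.

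The second is selection. Whether a man follows CPAP can be known only after randomisation, and it is also the quantity listed as an outcome. If men who do not follow CPAP are taken out and the rest are analysed per protocol, the outcome decides who contributes to its own comparison. The arms are then no longer the randomised arms, and a difference in adherence between them, or the lack of one, cannot be credited to the programme.

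At stake is one secondary outcome. It has some wider use, because both arms receive CPAP and adherence helps in reading the sleepiness scores and the AHI, which is measured with the device off.

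**Working it through.** **1. Does a baseline value exist?**

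| Step | When | Section |
|---|---|---|
| Baseline examinations | Visit 1 | Recruitment, Enrollment, and Procedure; Table 1 |
| Randomisation | Visit 2 | same |
| First CPAP titration | Visit 3 | same |
| Adherence data | From home device use, so after visit 3 | Measurements and Examinations |

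The population is newly diagnosed and other OSA treatment is excluded, so there is no earlier CPAP use to stand in for a baseline. The change score (post minus baseline) and the paired test both lack their first term. An unpaired comparison of on-treatment levels lacks nothing and can be run.

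**2. The plan's own figure.** The article gives no number for adherence. Its sample size rests on AHI: a difference of 8 with SD 10, 80% power and α = 0.05. Read as a between-group difference, n = 2 × (1.96 + 0.84)² × (10/8)² ≈ 24.5, so 25 per group, as stated. The present point does not depend on this figure.

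**3. How much could a common cut-off attenuate the difference?** The assumptions are mine, because no threshold is given. Adherence is normal with SD 1, the control mean is 0 and the intervention mean is 0.5. Men below one cut-off c are removed from both arms. The cut-off removes a share q of controls; 30% and 80% are the ends of the non-adherence range cited in the Discussion, and 50% is an intermediate value.

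Mean of the men left: μ + φ(c − μ) / [1 − Φ(c − μ)].

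| q | c | Control mean | Intervention mean | Difference | Share of 0.5 |
|---|---|---|---|---|---|
| 30% | −0.524 | 0.348/0.700 = 0.497 | 0.5 + 0.236/0.847 = 0.779 | 0.28 | 56% |
| 50% | 0 | 0.399/0.500 = 0.798 | 0.5 + 0.352/0.691 = 1.009 | 0.21 | 42% |
| 80% | 0.842 | 0.280/0.200 = 1.400 | 0.5 + 0.376/0.366 = 1.527 | 0.13 | 26% |

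Retention, 1 − Φ(c − μ), also becomes unequal between control and intervention: 70% vs 85%, 50% vs 69%, and 20% vs 37%.

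**4. Is the direction fixed?** No. Control men can be removed only for CPAP; intervention men can be removed for CPAP or for tele-RHB. Take a limiting case with no true effect, in which compliance with the two components is perfectly correlated. Suppose the CPAP rule removes the lowest 30% of controls, and the two rules together remove the lowest 50% of the intervention arm. From the control-mean column above, the means of those left are 0.497 and 0.798. The difference is 0.798 − 0.497 = 0.30 SD in favour of tele-RHB, produced by selection alone. This case is extreme, but it shows that the bias can run either way.

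**The case against.** The list is a long one in a condensed article, and its lead-in may simply have been stretched over an item it does not fit. Since the article says adherence comes from home device monitoring, the natural intention is an on-treatment level. That is a fair reading and it would settle the first problem, but the sentence as written still needs correcting and the selection would remain. The exact metric, such as hours per night, may be in a fuller document, and its absence here is not part of this point.

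It can also be said that post-randomisation exclusion affects every outcome and is a general matter. True, but adherence is the one outcome that is itself a criterion for exclusion.

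Adherence is also a minor aim. It is absent from the objectives, the hypothesis and the Abstract's list of secondary outcomes, and the Discussion remark reports an opinion. This limits the weight of the point and does not remove it.

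A reader might infer more than the article supports:

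- *No test can be applied.* Only the change score and the paired test fail.
- *Both arms would show full adherence, so the effect would vanish.* That needs a yes/no measure with the same threshold as the exclusion rule, and no threshold is given. A continuous measure under a common cut-off is attenuated, not erased.
- *The bias must run towards no difference.* The extra tele-RHB criterion in the intervention arm prevents that conclusion.
- *Between 7.5 and 20 of 25 men per arm would be lost (0.30 × 25 and 0.80 × 25).* This assumes that a general range cited for OSA patients applies to monitored volunteers, and that each non-adherent man would be excluded.

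**Conclusion.** The point holds in two parts. A change from baseline in CPAP adherence cannot be computed, because CPAP first starts after both baseline and randomisation; this rests on the text alone. Adherence would also be compared in a sample selected after randomisation on adherence itself; this follows from the exclusion wording together with the per-protocol analysis, and nothing else in the article repairs it.

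The size of the distortion is unknown. The 56%, 42% and 26% figures rest on normality, a true 0.5 SD shift and one cut-off common to both arms, and they illustrate scale only. The net direction is uncertain. The matter should be corrected, but it concerns a secondary outcome and does not by itself threaten the main comparison.

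**What to change.** - Take CPAP adherence out of the change-from-baseline list and state it as an on-treatment level over the 12 weeks, from the device data.
- Compare it between arms with an unpaired analysis in all randomised men, whether or not they followed the protocol. Drop the paired test for this outcome.
- Reconcile the exclusion of men who do not follow the programme and CPAP protocol with the listing of adherence as an outcome. The two passages conflict, and the investigators must settle how they fit together.

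The cost is small but goes beyond wording. Devices are already monitored remotely in both arms, so no new measurement is needed. The analysis set for this outcome does change, and device data must be kept for men who stop following the protocol. Recruitment began in October 2021, so this includes any men already excluded whose data still exist.

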#### Intervention Group

Participants of the intervention group will undergo home-based 12-week tele-RHB program with regular teleconsultations via phone calls and emails at least 1-2 times a week with a physiotherapist. Teleconsultations will include telemonitoring and analysis of previously completed training sessions and the current course of the program; additionally, telecoaching for upcoming training sessions and motivation to continue the program will also be provided. Participants will also record the details of their completed training sessions during the intervention in a training diary and will regularly send it to the physiotherapist for evaluation. As previously stated, participants will receive a training brochure with a detailed description of the tele-RHB program and its components (Multimedia Appendix 1). Tele-RHB program will include nutrition, health-related lifestyle and behavior change recommendations, and a minimum of 5 times a week—each lasting 30 minutes—of moderate-intensity aerobic training; in addition, there will be 10 minutes of inspiratory and 10 minutes of expiratory muscle training with breathing devices (Threshold IMT and Threshold PEP) and 10 minutes of oropharyngeal exercise along with individually titrated CPAP therapy. After the completion of the 12-week tele-RHB program, participants should be motivated to continue performing this comprehensive rehabilitation program in home conditions during the 1-year follow-up, but without the regular remote supervision by a physiotherapist. This tele-RHB program was developed based on previous research or guideline recommendations for patients with OSA or cardiovascular diseases [6,29-36].

#### Control Group

Participants of the control group will undergo individually titrated CPAP therapy alone, throughout 12 weeks.

### Data Analysis

#### Statistical Analysis

TIBCO Statistica (TIBCO Software Inc) will be used for statistical analysis of the obtained data. Statistical analysis will be performed by a person blinded to the experimental conditions. The Shapiro-Wilk test will be used to assess the normality of the data obtained. To compare participants’ baseline and postintervention obtained data within the same group, a paired 2-tailed *t* test will be used for statistical analysis. When comparing the baseline and postintervention data of the participants between both groups, an unpaired *t* test will be used. The level of statistical significance will be set as *P*<.05. The acquired data will be securely collected on an encrypted external hard drive.

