### Objective

This study protocol describes the first-ever randomized controlled trial to solely evaluate the effectiveness of the tele-RHB program among male adults with moderate to severe OSA. This study aims to assess whether completing a comprehensive telerehabilitation program and CPAP therapy positively affects the severity of OSA, QoL, body composition and circumferences, exercise tolerance, lipid profile, and respiratory muscle and lung function. Our hypothesis is that a combination of tele-RHB program and CPAP therapy will be more effective in the reduction of OSA severity and improvement of QoL, body composition, exercise tolerance, lipid profile, as well as respiratory muscle and lung function, compared to CPAP therapy alone.

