#### Sample Size

A power analysis was performed based on a previous study by Hupin et al [37], and the expected improvement in AHI was estimated to be approximately 8 (SD 10) episodes per hour at the end of the program versus the baseline. The number of participants in each of the two groups (n=25), necessary to achieve such an effect size, was calculated by statistical analysis at 80% statistical power with α=.05.

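### The plan sets within-arm paired t tests beside the between-arm t test at one P<.05 threshold and does not say which decides efficacy; within-arm change cannot isolate tele-RHB

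*Protocol article*

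**What the plan says.** The Statistical Analysis section of the protocol article gives two tests. The first compares "baseline and postintervention obtained data within the same group, a paired 2-tailed" t test being the stated method. The second reads "When comparing the baseline and postintervention data of the participants between both groups, an unpaired" t test. One threshold covers both: "The level of statistical significance will be set as" P<.05. Neither test is called primary, supportive or descriptive. The second sentence refers to baseline and postintervention data, not to change, and contains no baseline adjustment, although the Primary Outcomes section defines every primary outcome as a change from baseline.

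Three other places bear on this:

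- **Entry and baseline.** Under Inclusion Criteria, men must "have newly diagnosed OSA with an AHI ≥15 episodes per hour". Under Recruitment, Enrollment, and Procedure, "On the first visit, patients will undergo polysomnography (PSG"), and its result decides who is approached. Table 1 shows no other PSG before treatment, so this recording is also the AHI baseline.
- **Aim and hypothesis.** The Objective section first states the aim without a comparator: "This study aims to assess whether completing a comprehensive telerehabilitation program and CPAP therapy positively affects the severity of OSA". Its closing hypothesis is comparative, against CPAP alone.
- **Sample size.** The expected effect is "estimated to be approximately 8 (SD 10) episodes per hour at the end of the program versus the baseline", and 25 men per group are derived "at 80% statistical power with α=.05".

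**The concern.** The randomised question is whether adding tele-RHB to CPAP does better than CPAP alone. A paired test in one arm asks something else: whether that arm moved from its own baseline. Two features of this trial can move both arms without any effect of tele-RHB.

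1. Both arms start CPAP. ESS and SF-36, both primary outcomes, can improve for that reason alone.
2. Men are selected on a PSG value that is then reused as the baseline. Some fall in AHI on repeat measurement is expected from regression to the mean. This applies to AHI and closely related PSG measures. It does not apply to body fat, walking distance or mouth pressures, on which nobody is selected.

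A significant paired test in the tele-RHB arm is therefore not evidence for tele-RHB, and a significant result in one arm beside a non-significant result in the other is not a test of the difference. The plan does not rule out either argument. Of its two tests, only the paired one is plainly a test of change, the quantity in which the primary outcomes are defined. At stake is a claim of benefit that randomisation does not support.

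**Working it through.** **1. The plan's own figure.** Inputs from the Sample Size section: effect 8, SD 10, two-sided α .05, power 80%. The two-sample normal formula gives n = 2(1.960 + 0.842)² × 10² / 8² = 24.5, so 25 per arm, as stated. With the t distribution, 25 per arm gives 79.1% power and 26 would be needed, a trivial difference. A paired calculation with the same inputs needs only 15. The stated n therefore matches a two-arm comparison, although the effect is worded as a change over time.

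**2. How often the misleading pattern arises when the arms do not differ.** Inputs: n = 25 per arm (protocol). SD of within-arm change 10 is an assumption, reading the protocol's SD that way. The common true change δ is varied, because the documents do not say how much both arms would change.

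Let p be the power of a paired two-sided t test: noncentral t with 24 degrees of freedom, noncentrality √25 × δ/10 = δ/2, critical value 2.064. The arms are independent, so P(tele-RHB significant, control not) = p(1 − p).

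| Common change δ (events/h) | p | p(1 − p) |
|---|---|---|
| 0 | 0.050 | 0.048 |
| 1 | 0.077 | 0.071 |
| 2 | 0.1605 | 0.1347 (13%) |
| 3 | 0.302 | 0.211 |
| 4 | 0.484 | 0.250 |
| 5 | 0.670 | 0.221 |
| 6 | 0.821 | 0.147 |
| 8 | 0.970 | 0.029 |

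The maximum of p(1 − p) is 0.25, at p = 0.5, which corresponds to δ of about 4.1 events/h (0.41 SD).

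In simulation (100,000 trials per setting; δ of 0, 3.9, 4 and 8), an unpaired t test on change scores rejected in about 5.0% of trials at every δ, that is 2.5% in the direction favouring tele-RHB. At its worst the within-arm pattern is 0.25 / 0.025 = 10 times as frequent.

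**3. How much regression to the mean could contribute by itself.** The documents give neither the AHI distribution nor its night-to-night variation, so both are assumed, with no treatment effect and selection at AHI ≥15.

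- *Normal model:* true AHI mean 20 to 30, SD 12 to 20, visit-to-visit SD 7.1 (so the SD of change is close to 10). The spurious fall is 1.0 to 2.1 events/h, and an arm is significant in about 8 to 18% of trials.
- *Log-normal model:* median 15 to 20, log SD 0.8, night-to-night correlation 0.7 to 0.8. The spurious fall is 1.5 to 3.1 events/h. The SD of change is about 19 to 27, so an arm is significant in only about 6 to 15% of trials.

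With p between 0.06 and 0.18, p(1 − p) runs from 0.06 × 0.94 = 0.06 to 0.18 × 0.82 = 0.15. The log-normal model has a much larger SD than step 2, so its falls must not be read into the table above.

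**The case against.** The strongest reply is that the trial is already comparative. The hypothesis in the Objective section and the purpose of the analyses in the Results section both set the combination against CPAP alone. The sentence directly after the paired test plans a between-group test, and 25 per arm follows from the two-sample formula. Reporting changes within each group beside a randomised comparison is common, and ranking the tests could be left to an analysis plan that is not shown. All of this is fair. It disposes of one tempting reading, that the protocol plans the paired tests as its efficacy tests or will infer benefit from one arm being significant and the other not. It says neither.

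A second tempting reading is that about half of null trials would mislead. The figure of 50% is 2p(1 − p) at its maximum. It counts both directions, and control significant with tele-RHB not significant cannot produce a false claim for tele-RHB. It also needs a common change near 4 events/h. At 8 events/h, the figure in the Sample Size section, the relevant direction falls to 3%.

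A third is that the qualifying PSG alone produces such rates. Under the assumed distributions it does not. Follow-up PSG is also recorded without CPAP in use (Measurements and Examinations), so one cannot assume that CPAP directly lowers the measured AHI.

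What remains is not merely something left to another document. The article itself fixes the paired tests, gives them the same threshold as the between-arm test, and words the between-arm test so that it could mean separate comparisons at each visit.

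**Conclusion.** The concern holds in limited form. The protocol states two kinds of test at one significance level without saying which carries the efficacy conclusion, and one kind cannot answer the trial's hypothesis. With no arm difference, the pattern that would wrongly favour tele-RHB arises in 13 to 25% of trials for a common change of 2 to 5 events/h, at most 25%, against 2.5% for a between-arm test in that direction. These figures assume an SD of change of 10, approximate normality and an equal true change in both arms. They are AHI-scaled; for another outcome the ratio of common change to its SD is what matters, and the documents give no such figures for ESS or SF-36. Regression to the mean alone makes an arm significant in about 6 to 18% of trials under assumed AHI distributions. The point merits correction because the wording leaves an unsupported inference available, not because the protocol commits to it.

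**What to change.** State in the Statistical Analysis section that efficacy conclusions rest only on the between-arm comparison of the postintervention value adjusted for its baseline (ANCOVA with treatment group and baseline value). This replaces the unpaired t test as now worded, fits the comparative hypothesis and the two-sample n of 25, and uses values already collected. Report within-arm mean changes with confidence intervals, labelled descriptive.

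The cost is wording and a standard model: no extra men, visits or measurements. What is given up is the inferential role of the within-arm P values.

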#### Primary Outcomes

Primary outcomes include changes from baseline in AHI, obtained from PSG; ESS score; SF-36 score; percentage of body fat; 6MWT distance; as well as MIP and MEP values.

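### The between-group t test does not say that it tests change from baseline and does not adjust for baseline; ANCOVA would settle the wording and gain precision at no cost in patients

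*Protocol article*

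**What the plan says.** All places are in the protocol article.

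- **Primary Outcomes** defines the outcomes as changes: "Primary outcomes include changes from baseline in AHI, obtained from PSG". Six further measures follow: ESS, SF-36, percentage of body fat, 6MWT distance, MIP and MEP. Secondary Outcomes uses the same definition.
- **Sample Size** takes an AHI improvement of "approximately 8 (SD 10) episodes per hour at the end of the program versus the baseline" and derives 25 per group "at 80% statistical power with α=.05".
- **Statistical Analysis** gives two comparisons. Within each arm it compares "baseline and postintervention obtained data within the same group, a paired 2-tailed" *t* test. Between arms it reads "When comparing the baseline and postintervention data of the participants between both groups, an unpaired" *t* test. The section mentions no change score and no baseline covariate.
- **Objective** states a between-arm hypothesis: the program plus CPAP against CPAP alone.
- **Recruitment, Enrollment, and Procedure**, with Table 1, schedules the same examinations before and after the 12 weeks for both arms. The baseline value of each primary outcome is therefore collected anyway.

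**The concern.** The trial's question is answered by the between-arm comparison, and the article leaves the quantity compared unclear. Change from baseline is clearly tested only within each arm, and a within-arm test cannot show that one arm did better than the other. The between-arm sentence can mean a test of baseline values plus a test of post-program values, or a test of the changes.

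Three things follow:

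- **Precision.** The two readings give different standard errors from the same patients, and neither uses the baseline as well as ANCOVA does.
- **Chance imbalance.** There are 25 patients per arm, the blocks are not stratified by severity, and entry AHI has a floor of 15 with no ceiling. A post-only test leaves any baseline difference in the estimate.
- **Choice after the fact.** With seven primary measures, a sentence that allows two analyses lets the choice be made once results are visible.

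A significance test of baseline values does not help. Under randomisation any baseline difference is due to chance, and the test neither measures nor corrects its effect on the result.

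**Working it through.** **Inputs.** From Sample Size: difference 8, SD 10, 25 per arm, alpha .05, power 80%. Not in the article, so assumed: the baseline-post correlation ρ (shown from 0.3 to 0.9), equal SDs at both visits, and whether 10 is the SD of change or of AHI values (both shown).

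**1. Reproduce the stated sample size.** For a two-sided, two-sample comparison, n per arm = 2(1.960 + 0.842)² × 10²/8² = 24.53, which rounds up to 25. This matches. Power at 25 per arm is 80.7% by the normal approximation and 79.1% by the noncentral t distribution. A one-sided test would need 20 per arm and a single-group paired test 15, so the stated number is that of a two-sided, two-arm comparison.

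**2. If 10 is the SD of change.**

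- SD of a post-program value: 10/√(2(1−ρ))
- Residual SD under ANCOVA: that value × √(1−ρ²) = 10√((1+ρ)/2)
- Power from the noncentral t with noncentrality 8/(SD × √(2/25)), on 48 df, or 47 df for ANCOVA

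Example at ρ = 0.7: the SDs are 12.91 (post), 10 (change) and 9.22 (ANCOVA). The standard errors are 3.65, 2.83 and 2.61, and the noncentralities 2.19, 2.83 and 3.07.

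| ρ | SD post | SD ANCOVA | Post-only | Change | ANCOVA |
|---|---|---|---|---|---|
| 0.3 | 8.45 | 8.06 | 90.6% | 79.1% | 93.0% |
| 0.5 | 10.00 | 8.66 | 79.1% | 79.1% | 89.2% |
| 0.7 | 12.91 | 9.22 | 57.4% | 79.1% | 85.2% |
| 0.8 | 15.81 | 9.49 | 41.8% | 79.1% | 83.1% |
| 0.9 | 22.36 | 9.75 | 23.6% | 79.1% | 81.1% |

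Post-only beats change below ρ = 0.5, equals it at 0.5 and loses above it. ANCOVA is highest in every row.

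**3. If 10 is the SD of AHI values.** The SD of change is 10√(2(1−ρ)) and the ANCOVA residual SD is 10√(1−ρ²).

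| ρ | SD change | SD ANCOVA | Post-only | Change | ANCOVA |
|---|---|---|---|---|---|
| 0.3 | 11.83 | 9.54 | 79.1% | 64.9% | 82.7% |
| 0.5 | 10.00 | 8.66 | 79.1% | 79.1% | 89.2% |
| 0.7 | 7.75 | 7.14 | 79.1% | 94.7% | 97.2% |

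**4. Validity check.** Under the assumptions of step 2, 20,000 simulated trials per setting at ρ = 0.3, 0.5 and 0.7 gave type I error of about 5% for all three tests and an estimated effect of about 8 for each. Simulated ANCOVA power was 92.5%, 88.4% and 84.7%, within one point of the formula.

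**5. What a chance imbalance does.** At ρ = 0.7 in step 2, the standard error of the baseline difference between arms is 12.91 × √(2/25) = 3.65 episodes per hour. An imbalance of that size shifts the expected post-only estimate by 0.7 × 3.65 = 2.6. It shifts the change-score estimate by 0.3 × 3.65 = 1.1 in the opposite direction. ANCOVA removes the shift.

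**The case against.** **The sentence may already mean change.** The preceding sentence uses nearly the same phrase for a paired test, which is a test of change. Carried over to the two arms, the phrase can mean that changes are compared, and the outcome definition supports that. This stands: the article is unclear, not plainly wrong. If change is meant, power is 79.1% when 10 is the SD of change, and ANCOVA adds 2 to 14 points over ρ = 0.9 to 0.3.

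**The large power losses are conditional.** A reader might infer that the trial is analysed on raw post-program values and so has only 24% to 57% power. That needs three things together: the post-only reading, 10 as the SD of change, and ρ of at least 0.7. The article establishes none of them. At ρ = 0.5 there is no loss against change, and at 0.3 post-only is the stronger of the two. If 10 is the SD of AHI values, post-only power stays at 79%. The equal-SD assumption is also approximate, because the entry threshold truncates AHI at baseline only.

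**Nothing here is invalid.** A reader might also infer that a post-only test is biased or misses the treatment effect. It does not: under randomisation it estimates the same effect as a test on change, as step 4 shows. Chance imbalance is error in the one trial at hand, not bias over repeated randomisations.

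**Covariate adjustment is often left to the SAP.** That is true, and silence would be no finding. But the article does name a test and the data it applies to, and that statement does not match the outcome definition. An SAP that followed it would carry the ambiguity forward.

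**Conclusion.** The point holds as one of unclear specification and avoidable loss of precision. The between-arm sentence does not identify change from baseline as the quantity tested, makes no use of the baseline as a covariate, and on its literal wording includes a baseline test that serves no purpose.

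ANCOVA has the highest power of the three analyses under both meanings of the SD and at every ρ tabulated. The recommendation therefore does not depend on which reading the authors intended. The size of the gain does. With 10 as the SD of change it is 2 to 14 points over a change-score test. Against a post-only test it runs from about 2 points at ρ = 0.3 to 28 at 0.7 and 57 at 0.9. All these figures rest on a difference of 8, 25 per arm, equal SDs and an assumed ρ.

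A separate question stays open: Sample Size describes 8 (SD 10) as improvement against baseline, yet 25 per group reproduces only when it is used as the difference between arms. ANCOVA does not settle that.

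**What to change.** Replace the between-group sentence in Statistical Analysis with:

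> The postintervention value will be compared between groups by ANCOVA with randomised group and the baseline value of the same outcome as covariate; the adjusted mean difference and 95% CI will be reported.

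Apply it to every outcome that has a baseline value. CPAP adherence, first observable after titration at the third visit, has none. Delete between-group significance tests of baseline data and describe baseline by arm instead. Say in Sample Size whether 10 is the SD of change or of AHI values.

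The cost is a change of wording and one degree of freedom, with no added patients, visits or measurements. Settle it before any outcome is compared by arm.
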